### Randomization and allocation concealment

Participants will be randomized into one of the study arms in a 1:1 ratio to receive treatment with gestrinone or placebo, stratified by center. According to an electronically predefined randomization list, participants will be assigned to a treatment group (RedCap, version 11.0.3). Participants are randomly allocated to one of the study arms, and neither the investigator nor the study participants influence the allocation of participants to the groups (blinding).

### Statistical analysis

Statistical analysis will be carried out by researchers independently. Summaries by treatment group will be provided using appropriate descriptive statistics for all study variables. Descriptive statistics such as mean ± standard deviation median (minimum-maximum) will summarize continuous variables. Categorical variables will be summarized as the proportions of each category. Graphical data presentation can also be used to summarize data. The values of the scores and indices will be compared with the baseline values (baseline = pre-treatment) using the paired t-test and Wilcoxon test. Changes in laboratory measurements and other secondary outcomes will be compared with the paired Wilcoxon test. Unless otherwise indicated, all statistical tests will be interpreted at a nominal (i.e. no multiplicity adjustment) two-tailed significance level of 0.05 and all CIs at a nominal two-tailed 95% level. The safety and exploratory efficacy outcomes results will be used for analyses.

The Intention-To-Treat (ITT) and Per Protocol (PP) population will assess all safety and exploratory efficacy endpoints. The ITT population consists of all randomized participants who received the subdermal implant. The PP population includes only participants who complete all research procedures and do not present significant protocol violations, including breach of inclusion criteria.

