#### Other exploratory objectives

To compare the use of gestrinone subdermal bioabsorbable pellet versus placebo pellet on participant satisfaction, change in pelvic pain intensity, use of pain relief medication, uterine bleeding pattern and quality of life. Additionally, the pharmacokinetic profile (PK) of gestrinone will be characterized in a subgroup of participants.

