### Patients

The study will enroll 100 women with refractory pain control who underwent surgery for endometriosis at least 3 months ago and who had a histologically confirmed diagnosis of deep infiltrative endometriosis. Eligible participants are women with pelvic pain secondary to endometriosis surgically treated with refractory symptoms, independent of pain intensity. .Endometriosis-associated pelvic pain includes dysmenorrhea, dyspareunia, dysuria, dyschezia, and nonmenstrual pelvic pain.

Study participants have a medical history of indication for surgery as an option to reduce endometriosis associated-pain after having been failed to standard hormone treatment (combined hormonal contraceptives, progestogens, GnRH agonists or GnRH antagonists). Surgeries were conducted to fully eliminate endometriotic lesions from both the posterior compartment and anterior compartment, as well as from bowel compartment whenever present.

Detailed eligibility criteria are listed in Table 1.

**Table 1. t0001:** Study eligibility criteria.

Inclusion criteria
1. Willingness to provide informed consent
2. Woman aged between 18 and 50 years
3. Body weight between 50 ± 5 kg and 90 ± 5 kg
4. Pelvic pain secondary to endometriosis surgically treated with refractory symptoms, independent of pain intensity
5. Deep infiltrative endometriosis documented by biopsies (histopathological examination)
6. Last endometriosis surgery at least 3 months before randomization
7. Not planning to become pregnant within 12 months after the screening visit or be surgically sterilized
8. Absence of changes in the breast (BI-RADS 1 and BIRADS-2 classification) documented by an imaging report (mammogram for women aged > 40 years or bilateral breast ultrasound for women aged < 40 years) performed less than 12 months before randomization
9. Agreement not to use other hormones (estrogens, androgens and progestins) in any pharmaceutical form during the study
Exclusion criteria
1. Chronic severe disorders, including metastatic malignancies, end-stage renal disease with or without dialysis, clinically unstable heart disease, or any other disorder that, in the opinion of the investigator, excludes the participant from the study
2. Suspected or confirmed diagnosis of immunodeficiency based on medical history and/or physical or laboratory examination

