### Secondary safety outcomes [timepoints: pre-pellet insertion assessment, 3 and 6 months after gestrinone or placebo pellet insertion]

The main secondary safety outcome will be defined as the number of participants who experience androgenization defined by:Hirsutism: defined by Ferriman-Gallwey Score ≥ 8Clitoromegaly: defined by Clitoral index ≥ 35 mm^2^Acne: defined by the IGA scale (Investigator’s global assessment) grade 5 – severe inflammatory acne dominates the area, and there are many comedones, pustules, papules, and cystic acneAlopecia with sequelae of scalp thinningDeepening of the voice

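### The only tests the article states are paired comparisons with baseline, and none addresses gestrinone versus placebo

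*Protocol article*

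**What the plan says.** The Statistical analysis section names two sets of tests:

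- Scores and indices: "The values of the scores and indices will be compared with the baseline values (baseline = pre-treatment) using the paired t-test and Wilcoxon test".
- Laboratory and other secondary outcomes: "Changes in laboratory measurements and other secondary outcomes will be compared with the paired Wilcoxon test".

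Treatment group appears once: "Summaries by treatment group will be provided using appropriate descriptive statistics for all study variables". The section also sets a two-sided 5% level and 95% confidence intervals, both without multiplicity adjustment. It does not say which quantity the intervals are for.

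The aims are partly comparative. Other exploratory objectives begins "To compare the use of gestrinone subdermal bioabsorbable pellet versus placebo pellet on participant satisfaction, change in pelvic pain intensity" and goes on to analgesic use, bleeding and quality of life. The Discussion describes the trial as a comparison of the pellet's safety with placebo. The design supports such a comparison: "Participants will be randomized into one of the study arms in a 1:1 ratio to receive treatment with gestrinone or placebo, stratified by center".

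Secondary safety outcomes are counts of participants with an event: "The main secondary safety outcome will be defined as the number of participants who experience androgenization defined by" five listed components. The primary outcome, the percentage of women free of serious adverse events at 6 months, has no named test.

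**The concern.** A paired test against baseline asks whether values moved over time. It does not ask whether they moved more on gestrinone than on placebo.

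The distinction matters here because every woman also receives LNG-IUS 12. Study design gives it a contraceptive role, but the Introduction lists the LNG-IUS among hormone treatments for endometriosis. Pain, bleeding and quality of life could therefore change in both arms whatever gestrinone does. The placebo arm is there to remove that shared change, and the stated tests make no use of it.

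The same gap affects harm. If androgenization is tested only against baseline, the result cannot separate cases due to gestrinone from cases that would have been recorded on placebo as well.

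**Working it through.** **Inputs from the article.** "The study will enroll 100 women with refractory pain control", allocated 1:1, gives 50 per arm. The Discussion's possible 10% dropout gives 50 × 0.9 = 45. The level is two-sided 0.05. The article states no power, effect size, SD or event rate, so 100 cannot be reproduced, and the check concerns only what the named tests would deliver.

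**Assumptions.** The true gestrinone–placebo difference is zero. Both arms share a mean change from baseline of 0 to 0.8 SD of change. The documents give no value, so a range is shown.

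**1. Continuous scores.** The table gives 20,000 simulated trials per row, with a paired t-test in each arm and a two-sample t-test on change between arms.

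| n per arm | Common change (SD) | Gestrinone significant vs baseline | Gestrinone significant, placebo not | Between-arm test significant |
|---|---|---|---|---|
| 50 | 0 | 5.1% | 4.8% | 5.1% |
| 50 | 0.2 | 28.6% | 20.7% | 5.4% |
| 50 | 0.3 | 55.6% | 25.1% | 4.6% |
| 50 | 0.5 | 93.4% | 6.0% | 4.9% |
| 50 | 0.8 | 100% | 0.0% | 4.7% |
| 45 | 0.2 | 26.0% | 19.2% | 5.1% |
| 45 | 0.3 | 49.7% | 25.0% | 4.9% |
| 45 | 0.5 | 90.6% | 8.3% | 4.8% |
| 45 | 0.8 | 100% | 0.1% | 5.0% |

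Noncentral-t check at n = 45: power against baseline is 0.503 for a change of 0.3 SD and 0.976 for 0.6 SD.

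If each arm is significant with probability p, gestrinone alone is significant with probability p(1 − p). The maximum is 0.25, at p = 0.5:

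- 0.3 SD: 0.503 × 0.497 = 0.25.
- 0.6 SD: 0.976 × 0.024 = 0.023.

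So 25% is a ceiling, not a typical value (the 25.1% in the table is simulation error).

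**2. Androgenization.** Exclusion criterion 23 in Table 1 removes hirsutism, clitoromegaly, grade 5 acne and alopecia at randomization. Voice, the fifth component, is judged against the baseline recording. Baseline status is thus essentially *absent*, and a paired comparison can move only one way.

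With k new cases and none at baseline, all k non-zero differences are equal and tied. The normal-approximation Wilcoxon then gives z = √k, the same as asymptotic McNemar. The exact (sign) version gives p = 2 × 0.5^k.

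| New cases of 50 | Wilcoxon, approximate p | Exact p |
|---|---|---|
| 5 | 0.025 | 0.0625 |
| 6 | 0.014 | 0.031 |
| 8 | 0.0047 | 0.0078 |

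None of these depends on the placebo count. Fisher's exact test between arms does: 6 v 6 gives p = 1.0, 6 v 0 gives 0.027, and 8 v 1 gives 0.031. The counts are illustrative.

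**3. What a between-arm test could detect.** For 80% power the standardized difference is (1.96 + 0.84) × √(2/n): 0.56 at 50 per arm and 0.59 at 45.

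**The case against.** The best defence is that this is a condensed article about a safety-focused phase II trial. The primary and secondary safety objectives are worded as evaluations without a comparator, and the explicit comparative objective is exploratory. Summaries by arm are promised for all variables, so the arms will be seen side by side. The Discussion leaves firm conclusions to larger trials. For rare serious adverse events in about 50 women per arm, proportions by arm are a reasonable presentation.

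Much of this stands, and it rules out several stronger readings that a reader might infer:

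- *The trial never tests gestrinone against placebo.* This cannot be known, because a statistical analysis plan may exist and is not shown. The article states no such test.
- *The paired tests are run separately in each arm.* The text does not say so. Pooling the arms would be no better, since a pooled test contains no treatment contrast.
- *A paired Wilcoxon cannot be applied to binary data.* It can be computed, and it reduces to a sign or McNemar test. The trouble is the question it answers. If its sentence is read as covering only measured changes, androgenization has no stated test at all.
- *The primary outcome has the wrong test.* It is given none.
- *Regression to the mean guarantees improvement.* Entry does not depend on pain intensity, so no pain threshold selects high baseline scores. The argument rests on the shared LNG-IUS, and no figure in the article says how much that device changes pain.
- *Naming both a t-test and a Wilcoxon test without a rule is an error.* That choice is commonly left to the analysis plan.

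The defence does not remove the core. The article fixes named tests and a significance level, and those tests do not answer its own comparative objective. Descriptive summaries by arm carry no stated estimate of the difference.

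**Conclusion.** The point holds, and the section should be corrected. The article assigns paired baseline comparisons as its only stated tests and gives no test or effect estimate for gestrinone versus placebo, although Other exploratory objectives and the Discussion both claim that comparison. This is a method fixed badly, not a detail left out.

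With no true difference, 45 to 50 per arm and a shared change of 0.2 to 0.8 SD, the gestrinone arm is significant against baseline in about 26% to 100% of trials. Significance on gestrinone alone occurs in about 0% to 25%, depending on the size of the shared change. A between-arm test holds at about 5% throughout. For androgenization, the paired test asks only whether new cases exceed zero. The change sizes and event counts are assumptions; the form of the tests, the shared LNG-IUS and the baseline exclusions come from the article.

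**What to change.** In Statistical analysis, make the between-arm estimate with a 95% confidence interval the inferential analysis:

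- **Scores and laboratory values:** a difference between arms adjusted for baseline value and for center as the randomization stratum. ANCOVA, a mixed model over the visits or a rank-based equivalent would each serve.
- **Androgenization and laboratory events:** a risk difference with an exact or score interval.
- **Primary outcome:** the SAE-free percentage by arm, with the same type of interval.
- **Within-arm change from baseline:** descriptive only, without p-values.

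The change needs no new patients, visits or measurements, because baseline values and center are already recorded. It does need a dated record. Study design put the last visit at April 2025 and the article appeared in July 2025, so the change must be documented as made before unblinding. If that is no longer possible, the between-arm analysis should be labelled as added afterwards.

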## Discussion

Pelvic pain is of multifactorial origin, in which endometriosis is the leading cause. It is challenging to treat endometriosis and there are surgical and hormonal treatments available with variable endpoints. Post-surgery recurrence rate of painful symptoms is high and alternative hormonal methods are needed. Gestrinone is one of the clinical options to reduce endometriosis-associated pelvic pain, but data from clinical controlled trials, particularly with subcutaneous pellets, are scarce.

This will be the first multicenter randomized controlled trial to compare the safety of gestrinone subdermal bioabsorbable pellet versus placebo in women with endometriosis who underwent surgery without satisfactory response. This is the first to thoroughly evaluate the possible benefits of such a novel gestrinone pharmaceutical formulation with low-dose levonorgestrel-releasing intrauterine system (LNG-IUS 12) and might improve clinical outcomes in this population.

The study protocol has several innovations such as the participation of a patient representative as member of the Trial Steering Committee. Participant representative provided information about the burden of the disease and the impact of the treatment through a patient perspective that enabled the inclusion of patient-reported outcomes in the study protocol. The trial will use advanced technology for data collection to capture participant′s responses, as well as clinical and biological data. In addition, the study includes a variety of biochemical analyses, including an extension phase that will provide crucial information on the long-term use of gestrinone pellets and PK analyses by LC-MS/MS.

Since it is a safety-focused study, the trial has an experienced and independent Data Safety Monitoring Board and Clinical Events Classification Committee to evaluate all possible events blindly.

We acknowledge some limitations of the study. Given the possible 10% dropout rate, the sample size might be small. However, given that it is a safety-focused phase II study, results might serve as a basis for large clinical trials powered enough to conclude the safety and efficacy of gestrinone pellets in patients with pelvic pain due to endometriosis. Another limitation of the GLADE trial was not excluding concomitant adenomyosis at screening. There is a need for future studies to evaluate the efficacy of gestrinone with more precise endometriosis phenotype including concomitant adenomyosis.

In addition, the target population of GLADE trial is women with endometriosis-associated pelvic pain refractory to surgical treatment, independent of the surgical approach. The potential heterogeneity concerning surgical approaches, preferences and techniques performed at multiple Brazilian centers of expertise in endometriosis will be equilibrated between treatment groups by electronic randomization. Further larger studies addressing the efficacy of subdermal pellet of gestrinone and the potential differences of this effect on anterior, posterior or bowel compartment as well as on adenomyosis would bring evidence of a therapeutic option for pelvic pain.

## Conclusion

Gestrinone is used for the treatment of pain in women with endometriosis. Still, there is a lack of data from well-designed randomized clinical trials evaluating such a strategy using a subdermal pellet with a particular focus on safety. We expect the current study will provide high-quality evidence of therapeutic efficacy and foster future studies to further characterize subdermal pellets of gestrinone as a therapeutic option for endometriosis-related pelvic pain.

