**Methods:**

One hundred participants with documented deep infiltrative endometriosis who underwent surgery without satisfactory response will be randomly assigned (1:1) to either gestrinone 85 mg subdermal bioabsorbable pellets or placebo. Both arms will receive levonorgestrel-releasing intrauterine system (LNG-IUS 12). The treatment duration will be 6 months, with baseline, 3 months and 6 months clinical visits. The primary endpoint is a combination of serious adverse events (SAEs) accumulated within 6 months of insertion of the gestrinone or placebo pellet and collected through spontaneous reports and clinical findings. They include death, threat or risk to life, need for hospitalization, prolongation of pre-existing hospitalization, permanent disability or damage, congenital anomaly; or significant medical occurrences such as venous thromboembolism. The primary safety outcome will be the percentage of patients who do not experience SAEs 6 months after randomization. Androgenization, changes in laboratory exams and in pelvic pain intensity as well as quality of life (SF-36 and EHP-30 questionnaires) will be further evaluated. Daily data on uterine bleeding patterns and the use of pain relief medication will be remotely collected using an App. Pharmacokinetics profile of gestrinone pellet will be characterized.

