## Introduction

Pelvic pain is a disabling condition for women of reproductive age, negatively impacting their quality of life and work efficiency. Doctors frequently neglect it despite its estimated worldwide prevalence ranging from 5.6 to 26.6 [1,2]. Pelvic pain is considered a symptom of multifactorial origin in which endometriosis is the leading gynecological cause that affects 5–10% of women in their reproductive years. It means around 176 million women with endometriosis worldwide [3].

Surgical and hormonal treatments with variable endpoints are available and are still considered a significant challenge for medicine. Recommendations from different medical guidelines for managing the disease include surgery or a combination of surgical and pharmacological strategies [4–6]. Hormone therapy includes progestogens, anti-progestogens, combined oral contraceptives, gonadotrophin releasing hormone (GnRH) agonists, GnRH antagonists, the levonorgestrel intrauterine system (LNG-IUS), danazol and aromatase inhibitors. The choice of treatment for endometriosis must consider the severity of the symptoms, extent, and location of the lesions, comorbidities, age, intention to become pregnant, adverse drug events, and contraindications. Surgical treatment is indicated in the case of severe and disabling symptoms without improvement after the pharmacological treatment. However, post-surgery recurrence rate of painful symptoms is 21.5% after 2 year and 40–50% after 5 years of the surgery [4–6]. The direct costs for treatment of endometriosis are significant. The Brazilian Unified Health System (SUS) in 2021 registered 26,400 medical appointments and 8,000 hospitalizations for endometriosis with limited access to multifunctional teams specialized in endometriosis and longtime waiting for a surgery [7]. In this context, pharmacological treatment for endometriosis is prominent.

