**Figure 2. F0002:**
[figure not shown]
Study design.

Participants eligible for the main stage of the study will be randomized into one of the treatment arms:Experimental: Insertion of the levonorgestrel-releasing intrauterine system (LNG-IUS 12, Kyleena^®^) and gestrinone subdermal bioabsorbable pellet (85 mg)Comparator: Insertion of the levonorgestrel-releasing intrauterine system (LNG-IUS 12, Kyleena^®^) Kyleena^®^ levonorgestrel-releasing intrauterine system and subdermal implant of placebo bioabsorbable pellet

The insertion of the levonorgestrel-releasing intrauterine system (LNG-IUS 12, Kyleena^®^) is necessary as a contraceptive method for all study participants. LNG-IUS (LNG-IUS 12) has been developed for up to 5 years of use with an average release rate of ∼12 μg/24 h over the first year [21]. Clinical assessments will be recorded at recruitment (baseline), 3 and 6 months after pellet insertion. Assessment of the primary outcome will be carried out 6 months after insertion of the gestrinone pellet.

Participants will be invited to an extension phase (open-label) of the study to provide additional long-term safety data (EXT-PK). A subgroup of 15 participants at the end of 6 months of the main stage of the study who accept to participate in the extension phase will receive an insertion of a gestrinone pellet (85 mg), and the serum concentration of gestrinone will be monitored to characterize its pharmacokinetic profile (PK). Clinical assessments will be recorded at recruitment (baseline), 1, 3 and 6 months after pellet insertion. Blood sampling for PK study will be conducted.

Bioabsorbable gestrinone pellets are produced and marketed by Biòs Farmacêutica following standardized procedures and current legislation. Pellets containing a placebo will be prepared under the same conditions as those containing the product ingredient. Biòs Farmacêutica will donate all pellets used in this study.

GLADE is an investigator-initiated project. Biòs Farmacêutica funded the trial but was not involved in the study design, data collection, analysis, interpretation, writing of the manuscript, or decision to publish. The Trial Steering Committee designed the study protocol and is monitoring the trial’s progress. The first draft of the manuscript was written by the first and the last author and revised based on comments from all the authors. No writing assistance was provided.

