#### Insertion of the investigational product or subdermal bioabsorbable placebo pellet

The investigator will conduct the procedure in an outpatient setting. After local anesthesia, a small incision (4–5 mm) will be made, through which the pellet will be inserted under the skin of the buttock using a trocar. It will be performed just after the insertion of the LNG-IUS 12, and the randomization procedure.

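### Both arms start LNG-IUS 12 with the pellet, so the trial can show only an add-on effect of gestrinone; paired tests against baseline cannot isolate it, and the Conclusion claims too much

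*Protocol article*

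**What the plan says.** **Background treatment.** The Abstract (Methods) states: "Both arms will receive levonorgestrel-releasing intrauterine system (LNG-IUS 12". Under Study design, the device "is necessary as a contraceptive method for all study participants". The Introduction's list of hormone therapies for endometriosis includes "GnRH antagonists, the levonorgestrel intrauterine system (LNG-IUS), danazol and aromatase inhibitors". On timing, the section on pellet insertion says: "It will be performed just after the insertion of the LNG-IUS 12, and the randomization procedure". Table 1 (exclusion 20) bars women who still have an intrauterine device in place, so every device is newly inserted for the trial.

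**Efficacy aims.** Efficacy appears under Other exploratory objectives: "To compare the use of gestrinone subdermal bioabsorbable pellet versus placebo pellet on participant satisfaction", followed by pelvic pain, analgesic use, bleeding and quality of life. The endpoint section also labels efficacy exploratory.

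**Analysis.** The Statistical analysis section gives summaries by treatment group. For scores and indices it names the paired t-test and Wilcoxon test against pre-treatment values. For changes in laboratory measurements and other secondary outcomes it names the paired Wilcoxon test. Tests are two-sided at a nominal 0.05 without multiplicity adjustment.

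**What is promised.** The Conclusion says: "We expect the current study will provide high-quality evidence of therapeutic efficacy". The Discussion calls the trial a safety-focused phase II study, concedes that the sample might be small, and says its "results might serve as a basis for large clinical trials powered enough to conclude the safety and efficacy of gestrinone pellets".

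**The concern.** Three features combine. The background device is presented only as contraception, although the article itself counts it as a treatment for the disease. It starts in the same session as the pellet, so the 3- and 6-month values carry the onset of both. And the tests named for scores compare each woman with her own baseline, which is the comparison that a co-started treatment distorts.

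A fall in pain or a gain in quality of life in the gestrinone arm could then be credited to the pellet when part or all of it comes from the device, from placebo response or from regression to the mean. The Conclusion's wording invites that reading. The limitations in the Discussion cover sample size and dropout, adenomyosis and surgical heterogeneity, but not the co-started LNG-IUS.

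**Working it through.** The article gives N = 100 without a power statement, effect size or SD, so there is no planned figure to reproduce. The calculation below is an illustration.

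**Inputs from the article.** N = 100 at 1:1 gives 50 per arm. The possible 10% dropout gives 50 × 0.9 = 45 per arm. Alpha is 0.05 two-sided. The VAS runs from 0 to 10 cm.

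**Assumed inputs (not in the article).** SD of the VAS change is 2 to 3 cm. The LNG-IUS effect L is 0.5 to 2 cm. VAS pain is treated as one of the scores to be tested.

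**Step 1: what each comparison estimates.** Let G be the effect of gestrinone in women who also have the LNG-IUS, L the LNG-IUS effect, P the placebo response and R regression to the mean.

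- Expected change, gestrinone arm: G + L + P + R
- Expected change, placebo arm: L + P + R
- Between-arm difference: G
- Paired test in the gestrinone arm: tests G + L + P + R = 0, not G = 0

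**Step 2: paired test when G = 0.** Take P = R = 0, so that only the LNG-IUS acts. By normal approximation, the probability of a significant improvement is Φ(L / (SD/√n) − 1.96). With n = 45, SD = 2.5 and L = 1: SD/√n = 2.5/6.708 = 0.373; 1/0.373 = 2.683; Φ(2.683 − 1.96) = Φ(0.723) = 0.765.

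| LNG-IUS effect | SD 2 | SD 2.5 | SD 3 |
|---|---|---|---|
| 0.5 cm | 38.9% | 26.8% | 20.0% |
| 1 cm | 91.8% | 76.5% | 60.9% |
| 1.5 cm | 99.9% | 98.1% | 91.8% |
| 2 cm | about 100% | about 100% | 99.4% |

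**Step 3: simulation.** 20,000 trials, n = 45 per arm, SD 2.5, G = 0, t-tests:

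| LNG-IUS effect | Paired test, gestrinone arm | Between-arm test |
|---|---|---|
| 0 cm | 5.0% | 5.0% |
| 1 cm | 74.3% | 4.8% |
| 2 cm | about 100% | 5.1% |

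The simulated 74.3% agrees with the approximate 76.5%. The between-arm test holds its level whatever the device does.

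**Step 4: precision of the valid contrast.** The standardised difference detectable with 80% power is (1.960 + 0.842) × √(2/45) = 0.59, which is 1.18 cm at SD 2 and 1.77 cm at SD 3. Power for a 1 cm add-on effect is 66%, 48% and 35% at SD 2, 2.5 and 3. The right comparison is therefore unbiased but imprecise, which suits exploratory wording.

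**Step 5: the texts side by side.** The objectives and the endpoint section call efficacy exploratory. The Statistical analysis section makes no multiplicity adjustment. The Discussion leaves efficacy conclusions to larger, adequately powered trials. The Conclusion's expectation does not fit with these.

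**The case against.** The strongest reply is that a background treatment given equally to both arms of a randomised, blinded trial does not bias the comparison between them. That is right, and Step 3 confirms it. A reader might infer that the LNG-IUS makes sound efficacy evidence impossible. The documents do not support that: it narrows the question to an add-on effect, and may leave less pain for the pellet to relieve, but the between-arm estimate stays valid.

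The combination is also disclosed. The Abstract and Study design state it, the exploratory objective names the placebo pellet as comparator, and the Discussion speaks of benefit together with the LNG-IUS. The reported embryotoxicity of gestrinone supports the contraceptive reason. All of this stands. What is absent is the add-on qualifier in the objective and Conclusion, and the LNG-IUS among the limitations.

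A full analysis plan may well contain a between-arm test, and its absence from an article is not the complaint. The complaint concerns what the article does fix, namely paired tests against baseline as the named inference for scores.

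It can also be said that the Conclusion's phrase is an expectation and would overreach even without the device. That is true; the overreach is a separate strand and needs its own correction.

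Two further inferences fail. A reader might think that device-related serious events bias the safety comparison. Occurring equally in both arms, they leave the difference in SAE-free percentage essentially unchanged. A reader might also infer from Table 1 that women without earlier hormone failure are being enrolled. The Patients section says that participants had failed standard hormone treatment, and silence in a condensed table is weak evidence against it.

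**Conclusion.** The point holds in this form. The trial can validly estimate the effect of gestrinone added to newly inserted LNG-IUS 12, but not of the pellet alone. The paired tests named in the article do not isolate even the add-on effect. With no gestrinone effect, a 1 cm LNG-IUS effect would produce a significant within-arm improvement in about 61% to 92% of trials for an SD of 3 down to 2 cm (n = 45), against about 5% for a between-arm test (simulated at SD 2.5 cm). For a 0.5 cm effect the range is 20% to 39%.

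These sizes rest on the assumed SD and LNG-IUS effect. The direction of the error needs only that the device, placebo response or regression to the mean improves scores. The conflict between the Conclusion and the rest of the article rests on the text alone. Randomisation, blinding and the primary safety comparison are not called into question.

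**What to change.** - **Statistical analysis:** make the between-arm difference in change from baseline the basis of every efficacy statement, for example adjusted for the baseline value and stratified by center as in the randomisation. Keep the paired within-arm tests as description only.
- **Other exploratory objectives and Conclusion:** describe the result as exploratory, hypothesis-generating evidence on gestrinone added to LNG-IUS 12, in line with the Discussion.
- **Discussion, limitations:** state that the LNG-IUS was started together with the pellet in both arms, so the effect of the pellet alone cannot be inferred.

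No treatment, contraception, visit or eligibility rule changes. The last visit was estimated for April 2025, so these are analysis and reporting changes. The change of test should be dated and recorded, before unblinding if that is still possible. The cost is a few sentences, one between-arm model per endpoint and a more modest claim.
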